**7.1　Methods of data collection**

Data obtained at the Kaori Clinic and the Consortium for Dementia Prevention Activities are converted to PDF format by the person in charge, shared on Dropbox with a password set to protect personal data and sent to the principal investigator. Once the PDFs have been converted, the documents are promptly destroyed.

The principal investigator anonymizes the information (including personal data) and creates a correspondence table. The principal investigator stores the correspondence table between individuals and symbols on a computer sealed off from the outside world and on a USB memory stick (mobile media) in the Rehabilitation Department of Showa University Fujigaoka Rehabilitation Hospital. The anonymized Excel file will then be shared on a password-protected cloud with [name] in the Research Center for Advanced Science and Technology, The University of Tokyo, who will do random allocation and statistical analysis.

1. **Evaluations of efficacy**

**8.1　Primary outcome**

Primary outcome

Assessment of five cognitive domains by CogEvo®︎: spatial cognition, orientation, memory, attention and executive function.

Secondary outcome

1. Quality of life assessment using the SF36 questionnaire
2. Screening for the presence of dementia with the Japanese version of the Montreal Cognitive Assessment (MoCA-J)

**8.2　 Evaluation of Efficacy**

8.2.1.　Primary outcome

The intervention is deemed effective if there is a statistically significant difference in changes of CogEvo®︎ scores between the intervention and control groups.

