**3.4 Hypothesis**

Minami et al. have reported on the usefulness of personal computer (PC)-based attention training for patients with higher brain dysfunction in the chronic phase. Twenty-two patients were divided into a PC-based training group and a conventional drill-based attention training group. After a period of two months (eight sessions), the training methods were switched, resulting in a total intervention period of four months. The results showed that the values of the FIM/FAM cognitive items 'Problem Solving', 'Disability Adaptation' and 'Representation', and the behavioral assessment items 'Triggering' and 'Easy Fatigue' improved significantly after the attention training using the PC.^7)^ In the present study, cognitive rehabilitation with the iPad application SoroTouch may improve participants' cognitive functions, and scientific verification through RCTs is desirable.

1. **Objectives**

The present study is an exploratory clinical study. The subjects will be 20 middle-aged and older adults (40-79 years) and the effects on cognitive functions and quality of life (QOL) will be investigated after they perform SoroTouch for 30 minutes a day for 6 months. In the future, it is expected that SoroTouch will prevent dementia in patients with mild cognitive impairment (MCI).

1. **Details of the clinical research**

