**5.3** **Methods of case registration and allocation**

The principal investigator (co-investigator) explains the subject of the study in accordance with the explanatory document and, if consent is obtained, registers and allocates the subject as a research participant. Research participants will be given an identification code for anonymization purposes, which will be used as the identification code for research participants in this study.

The study will be conducted in a randomized comparison to ensure that the allocation does not result in differences in medical background between treatment groups. The participants will be allocated in a 1:1 ratio to the SoroTouch treatment group and the non-treatment group using Muzinwali (https://mujinwari.biz/users/login). The allocation method will be stratified block allocation with CogEvo®︎ (index below and above 70) as allocation factor. After obtaining consent from the study participants, investigators will access Muzinwali to confirm the allocation of the intervention to the study participants concerned. As soon as possible after confirming the allocation, the 'Allocation Instructions/Confirmation Form' is signed and dated. After obtaining consent from the research subject to participate in the research and conducting the allocation, the investigator in charge of the research should ensure that all 'allocation instructions/confirmation forms' are properly kept by the principal investigator.

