8.2.2.　Secondary outcome

The intervention is deemed effective if there is a statistically significant difference in changes of SF-36 or MoCA-J scores between the intervention and control groups.

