**10.2** **A target number of subjects and rationale for setting the number**

The target number of subjects: 20

［Rationale] Based on the results of the present study on cognitive function and quality of life, a larger-scale validation study is planned in the future. Therefore, this study is an exploratory study, and the number of patients was set at 20 which is the maximum number of patients that can be conducted at the relevant institution. If the intervention in this study has an effect size of 1.4 on the CogEvo change, the probability of error for Type 1 and Type 2 can be assessed as 0.05 and 0.2 respectively with 20 analysis subjects.

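### An exploratory study of 20 people, sized by feasibility, is written to declare the app effective on any statistically significant difference

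*Protocol*

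**What the plan says.** **Purpose and size.** Protocol section 4 (Objectives) states: "The present study is an exploratory clinical study". Section 10.2 repeats this and adds that, on the basis of these results, "a larger-scale validation study is planned in the future". It gives the reason for the sample size: "the number of patients was set at 20 which is the maximum number of patients that can be conducted at the relevant institution". It then attaches a power statement that is conditional on its opening words, "If the intervention in this study has an effect size of 1.4 on the CogEvo change"; under that condition it puts the two error rates at 0.05 (Type 1) and 0.2 (Type 2) for 20 people analysed. Neither a source for 1.4 nor a standard deviation is given. Under section 5.3 participants are "allocated in a 1:1 ratio to the SoroTouch treatment group and the non-treatment group", so 10 per arm.

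**Decision rules.** Section 8.2.1 reads: "The intervention is deemed effective if there is a statistically significant difference in changes of" CogEvo scores. Section 8.2.2 applies the same rule to "SF-36 or MoCA-J scores between the intervention and control groups". Neither rule names a direction or a minimum effect.

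**Analysis.** Section 10.5.2 compares change from baseline on five CogEvo domain scores by analysis of covariance at a significance level of 0.05. It does not state whether the test is one- or two-sided, and it states no adjustment for five scores. Section 10.5.3 plans an unpaired t-test for MoCA-J and SF-36.

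**The concern.** The protocol gives the study two roles that do not fit together. Sections 4 and 10.2 make it preparatory: it explores, its size is set by capacity, and validation comes later. Sections 8.2.1 and 8.2.2 make it decisive: one significant p-value settles that the app is effective. A team that follows the plan as written would have to report effectiveness from a study that the same plan describes as exploratory.

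Two features make that label weak. With 10 per arm only a large observed difference can be significant, so the results that earn the label tend to be those in which chance has enlarged the effect. The label is also easier to reach than a single test at 0.05 suggests, because the primary outcome has five scores and the secondary rule accepts either of two instruments. Read literally, a significant difference in favour of the control group would satisfy the rule too.

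The label would be public. Section 25 has the primary endpoint report published on jRCT, and section 19.1 says that the funder sells the app (while excluding it from subject selection, data acquisition and analysis).

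**Working it through.** **Inputs.** 20 analysed, 1:1, so 10 per arm (sections 5.3 and 10.2); effect size 1.4, taken as a standardised mean difference in change (10.2); Type 1 error 0.05 and Type 2 error 0.2 (10.2). Two-sided testing is assumed.

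**1. The plan's own figure.**
- Normal approximation: n per arm = 2 × (1.960 + 0.842)² / 1.4² = 15.70 / 1.96 = 8.01, rounded up to 9, or 18 in total.
- Exact noncentral t: 9 per arm gives 79.6% power and 10 per arm gives 84.1%. The smallest size reaching 80% is therefore 10 per arm, or 20 in total.
- A one-sided normal calculation gives 7 per arm (14 in total) and does not match.

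The figure of 20 reproduces as a two-sided calculation. The sample-size arithmetic is sound.

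**2. What must be observed for significance.** For an unadjusted t-test with 18 degrees of freedom, the smallest significant observed standardised difference is t(0.975, 18) × √(2/10) = 2.101 × 0.447 = 0.94. The half-width of the 95% confidence interval is also 0.94 SD, so the interval spans about 1.9 SD.

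**3. How large significant estimates are.** One million two-arm trials were simulated for each true effect, 10 per arm, keeping those with two-sided p < 0.05 in favour of the app. Only 1.4 comes from the protocol; the other true effects are assumptions.

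| True effect (SD) | Power | Mean significant observed standardised difference | Ratio to truth | Same trials, difference in true SDs | Ratio to truth |
|---|---|---|---|---|---|
| 0.3 (assumed) | 10% | 1.20 | 4.0 | 1.06 | 3.5 |
| 0.5 (assumed) | 18% | 1.24 | 2.5 | 1.11 | 2.2 |
| 0.8 (assumed) | 40% | 1.32 | 1.65 | 1.21 | 1.5 |
| 1.4 (section 10.2) | 84% | 1.60 | 1.15 | 1.52 | 1.09 |

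The observed standardised difference divides by the SD estimated in the trial, so it also carries chance underestimation of that SD. The last two columns remove this part.

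**4. Five domain scores.** Suppose there is no true effect and one significant domain score is enough. At one time point, the chance of at least one significant result in either direction is 1 − 0.95⁵ = 22.6% for independent scores (22.8% when simulated). Simulation with 10 per arm gives 21.0%, 19.0% and 15.2% for assumed correlations of 0.3, 0.5 and 0.7.

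**The case against.** The strongest reply is that this is a conflict of wording and that more is easily read into it than the protocol says. Several parts of the reply stand.

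- A reader might infer that an inflated estimate will be passed on to size the validation study. Section 10.2 says only that the larger study is planned on the basis of these results. It does not say that the observed effect will set its sample size, or that only a significant estimate would be used.
- A reader might infer that a non-significant result will be reported as showing no effect. The rules give only a sufficient condition for effectiveness, and nothing is said about the other case.
- A reader might object that no confidence interval is requested. Interval reporting is commonly left to the statistical analysis plan. Section 25 mentions such a plan, which is not at hand, so this is not counted as a fault.
- The overstatement is modest, 1.15 times, if the true effect is the protocol's 1.4. The larger ratios rest on assumed smaller effects.
- The t-test is not the planned primary analysis. If baseline is the covariate, the threshold in SDs of change would be roughly 0.97, 0.84 or 0.69 for assumed correlations between baseline and change of 0, 0.5 or 0.7.

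What does not stand is that the point can be left to the analysis plan. The effectiveness rules are fixed in the protocol itself, and section 10 requires the protocol to be revised if the analysis plan departs from it. A confidence interval added elsewhere would leave the verdict in 8.2.1 and 8.2.2 as it is. Nor does 1.4 remove the difficulty: section 10.2 introduces it as a condition and gives no source.

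**Conclusion.** The point holds as a conflict within the protocol. Sections 8.2.1 and 8.2.2 prescribe an effectiveness verdict that sections 4 and 10.2 do not set the study up to give. The fault lies in the decision rule, not in the sample-size calculation or the choice of tests.

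Under the t-test approximation with all 20 analysed, any significant favourable estimate exceeds a true effect below 0.94 SD, and on average significant estimates exceed larger true effects too. How far depends on the unknown true effect: from about 4 times at an assumed 0.3 to 1.15 times at 1.4. If baseline adjustment explains much of the change, the threshold falls, but with an assumed correlation of 0.7 it is still about 0.69 SD. The 15% to 23% chance of a false significant domain score assumes that one score suffices, which section 8.2.1 neither says nor excludes. Claims about the sample size of the next trial, or about how a non-significant result would be read, go beyond the text and form no part of this conclusion.

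**What to change.** Replace the effectiveness rules in sections 8.2.1 and 8.2.2 with:

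*Group differences in change will be reported with 95% confidence intervals; a statistically significant difference in favour of the intervention will be read as an exploratory signal to be tested in the planned validation study, not as proof of effectiveness.*

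This brings both sections into line with sections 4 and 10.2 and supplies the missing direction. The planned tests, sample size and assessments stay as they are. How the validation study is sized can be left to that study's own protocol.

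The cost is a wording change, with committee approval of the revised protocol under section 22.2. The downside is that the sponsor gives up an effectiveness claim from this study.

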8.2.2.　Secondary outcome

The intervention is deemed effective if there is a statistically significant difference in changes of SF-36 or MoCA-J scores between the intervention and control groups.

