5.1.2　Secondary outcome

Quality of life assessment using the SF36 questionnaire

Screening for the presence of dementia with the Japanese version of the Montreal Cognitive Assessment (MoCA-J)

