**10.5.2** **Analysis of primary outcomes**

Group differences in change from baseline on the five cognitive domains (spatial cognition, orientation, memory, attention and executive function) scores of the CogEvo ®︎ will be assessed by analysis of covariance. The significance level is set at 0.05. Missing values are complemented by the last observed value.

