**10.5.3** **Analysis of secondary outcomes**

The MoCA-J and SF36 scores will be compared between the two groups before and at 6 months after the start of Soroouch by an unpaired t-test.

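### Section 8.2.2 lets a secondary outcome alone earn the verdict that the intervention is effective, with no dependence on the primary result

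*Protocol*

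**What the plan says.** Protocol sections 5.1 and 8.1 rank the outcomes: CogEvo is primary, SF-36 and MoCA-J are secondary. Section 5.1.2 describes the first secondary outcome as "Quality of life assessment using the SF36 questionnaire".

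Section 8.2 gives the criteria for judging efficacy. For the primary outcome, the rule in 8.2.1 begins "The intervention is deemed effective if there is a statistically significant difference in changes of", and the instrument it then names is CogEvo. For the secondary outcomes, 8.2.2 says "The intervention is deemed effective if there is a statistically significant difference in changes of SF-36 or MoCA-J scores between the intervention and control". The two sentences differ only in the instruments named, and the second joins its two instruments with an 'or'.

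On analysis, section 10.5.2 states for CogEvo: "The significance level is set at 0.05". Section 10.5.3 covers both secondary instruments, which "will be compared between the two groups before and at 6 months after the start of Soroouch by an unpaired t-test". Neither section makes the secondary tests conditional on the primary, orders them or divides alpha. The sample size in 10.2 refers only to CogEvo. The Objectives section adds: "The present study is an exploratory clinical study".

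**The concern.** A primary outcome exists so that one pre-named result carries the trial's conclusion. Here the subject of both verdict sentences is the intervention, not the particular outcome, and the verdict is the same. A null CogEvo result together with a significant SF-36 or MoCA-J difference would therefore meet the protocol's own definition of an effective intervention.

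Two features add weight. The control arm receives no treatment (section 5.3), so participants will know their allocation, and SF-36 is a questionnaire. Section 10.2 also says the results will inform a larger validation study, so an unearned verdict would be carried forward.

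This cannot simply be left to a separate analysis plan. The protocol states the decision rule itself, and the opening of section 10 requires the protocol to be revised if the analysis plan departs from it.

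**Working it through.** **Inputs.** 20 participants, 1:1, so 10 per arm (sections 5.2.2, 5.3, 10.2). Alpha 0.05 (10.5.2, stated for the primary). Unpaired t-test for the secondary outcomes (10.5.3). Assumptions the protocol does not settle: two-sided tests, 0.05 for the secondary tests too, one test of change per instrument, and the correlation between outcomes, taken from 0 to 0.7.

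**The plan's own figure.** Section 10.2 supposes the intervention "has an effect size of 1.4 on the CogEvo change" and says "the probability of error for Type 1 and Type 2 can be assessed as 0.05 and 0.2 respectively with 20 analysis subjects".
- Normal approximation: n per arm = 2 × (1.960 + 0.842)² / 1.4² = 8.01, rounded up to 9, so 18 in total.
- Exact two-sided t-test: power 79.6% at 9 per arm and 84.1% at 10 per arm.

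So 20 is the smallest balanced total reaching 80%. The figure reproduces and is not in dispute.

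**False verdict with no true effect, independent outcomes.**
- Primary only, one CogEvo test: 0.05.
- Either secondary, ignoring the primary: 1 − 0.95² = 0.0975.
- Any of CogEvo, SF-36 and MoCA-J: 1 − 0.95³ = 0.143.
- CogEvo null and either secondary significant: 0.95 × 0.0975 = 0.093.
- CogEvo null and SF-36 significant: 0.95 × 0.05 = 0.048.

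**Correlated outcomes.** Simulated t-tests with 10 per arm and equal correlation among the three outcomes give the other columns. The second row is the first minus 5.0%; the third is the second divided by 0.95.

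| Event, no true effect | Corr. 0 | Corr. 0.5 | Corr. 0.7 |
|---|---|---|---|
| Verdict by any of the three | 14.3% | 12.7% | 11.1% |
| Verdict with CogEvo null | 9.3% | 7.7% | 6.1% |
| Either secondary significant, given CogEvo null | 9.75% | 8.1% | 6.4% |
| CogEvo null and SF-36 significant | 4.8% | 4.1% | 3.5% |

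The rule as worded names no direction, so these rates count differences either way. By symmetry, the last row counting only differences that favour the app is half: 2.4%, about 2.0% and about 1.7%.

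**After the fix.** With the verdict reserved for a single CogEvo test, the first row is 5% and the second is zero by construction.

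**The case against.** The best defence is the heading. The sentence stands under Secondary outcome, parallel to Primary outcome, and may have been meant as a criterion for an effect on that outcome. The ranking is kept in 5.1, 8.1, 8.3, 10.5 and 10.6, and a separate primary endpoint report is planned. No text merges 8.2.1 and 8.2.2 into one overall verdict. So a reader who infers that the protocol abolishes its outcome ranking goes too far. What stands against the defence is the sentence itself: it deems the intervention effective, in the words used for the primary. If the narrower meaning was intended, the fix merely states it.

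The study is exploratory, and quality of life is among its objectives. Both points limit the seriousness. They justify measuring and reporting SF-36, but not giving it the primary's verdict. Sizing on the primary alone is ordinary practice and no defect.

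Some stronger readings are tempting but unsupported:
- A reader might infer that staff encouragement goes only to the app group and would bias SF-36. Section 13.1.2 mentions it after listing burdens for both arms and does not restrict it.
- A reader might take the roughly 8% to 10% rate for either secondary as applying whatever CogEvo shows. If the outcomes are correlated, the rate given a null CogEvo result falls to 6.4% at correlation 0.7.
- A reader might count eight SF-36 scales plus MoCA-J and reach 21% to 37%. The protocol does not say how many SF-36 scores are tested, so that figure rests on an assumption it does not make.
- A reader might infer that the company selling the app could exploit the rule. Section 19.1 excludes it from subject selection, data acquisition and data analysis.

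**Conclusion.** The point holds as a defect of wording in a decision rule. Taken literally, 8.2.2 permits a conclusion of effectiveness on SF-36 or MoCA-J when CogEvo shows nothing. With one two-sided test at 0.05 per instrument and no true effect, the overall false-verdict rate is about 11% to 14% instead of 5%. The part arising with a null CogEvo result is about 6% to 9%; SF-36 significance with CogEvo null occurs in about 3.5% to 5%. The lower ends belong to correlation 0.7 and the upper ends to independence.

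These figures count CogEvo as one test. How its five domains are combined is a separate question. The exploratory purpose keeps the matter moderate, but the correction is nearly free and changes what the trial may conclude.

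**What to change.** In section 8.2.2, replace the verdict sentence with wording such as: SF-36 and MoCA-J are supportive outcomes; between-arm differences in change are reported with 95% confidence intervals and interpreted alongside the primary result; they do not by themselves support a conclusion of effectiveness. Keep the verdict in 8.2.1 only.

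This is a text change. Sample size, visits, data collection and tests stay as they are. The one cost is that effectiveness can no longer be claimed on a secondary outcome alone.

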**8.3** **Method and timing of analysis of endpoints**

Primary outcome

After entry and initial assessment of study participants, eligible data will be analysed every month for a total of six months.

Secondary outcome

Data will be collected at the end of the evaluation period and MoCA-J and SF36 scores analysed between intervention and control groups.

1. **Evaluations of safety**

**9.1** **Safety assessment measures**

The principal (Co-) investigators evaluate the diseases and defects identified during the period described in '5.5 The expected period of participation of research participants'.

**9.2** **Methods and timing of evaluation, recording and analysis of safety measures**

Investigators will document in the medical record the time of onset and outcome of the disease or defect, severity, outcome, causal relationship to the study and the course of the disease or defect. The severity will be judged according to the following criteria, and the severity will be judged as 'serious' or 'non-serious' based on the criteria in section '9.4 Procedures for collecting, recording and reporting information on diseases and other conditions'.

[Criteria for determining severity]

1) Mild: No treatment is required and the patient recovers.

2) Moderate: Cases in which treatment is required to continue wearing the test device. Cases requiring additional treatment/procedure for post-operative diseases or defects.

3) Severe: Cases in which the continuation of the wearing of the test device is difficult.

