**9.4** **Procedures for collecting, recording and reporting information on diseases and other conditions**

When co-investigators obtain information on the following matters, they report it to the administrator of the implementing medical institution and the principal investigator within the respective timelines stipulated. The principal investigator reports the matter to the accredited clinical research review committee and promptly informs the other research assistants. Then, the other co-investigators will promptly report the matter to the administrator of the implementing medical institution. In addition, when the principal investigator obtains information on the matters in ① and ② (a), he will also report it to the Minister of Health, Labor and Welfare within the stipulated period of time.

①Predictable matters are those described in the study device summary, the study protocol or the consent document. The following diseases etc., the occurrence of which is suspected to be due to this study and which cannot be predicted.

[Reporting period] 7 days.

(a) Death.

(b) Diseases, etc. that may lead to death.

② The following matters in cases where this research is conducted.

[Reporting deadline] 15 days

(a) The following diseases, etc., which are suspected to be caused by this research (excluding those falling under 9.4 ①)

(1) Death

(2) Diseases, etc. that may lead to death

(b) The following diseases, etc., which are suspected to be caused by this research and cannot be predicted (excluding those listed in 9.4 ①)

(1) Diseases requiring hospitalisation or prolonged hospitalisation for treatment, etc.

(2) Disability

(3) Diseases, etc. that may lead to disability

(4) Illnesses, etc. that are serious enough to be related to illnesses (1) to (3) and death or illnesses that are likely to lead to death

(5) Congenital diseases or abnormalities in later generations

③ Diseases suspected to be caused by this research (excluding those listed in ① and ②).

[Reporting deadline] When periodic reports are made to the Authorized Clinical Research Review Committee.

When making reports on ① to ③ above, information should be provided to the company manufacturing the device at the same time.

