**22.2** **Changes to the research protocol**

The principal investigator will revise the research protocol if it is deemed necessary to do so. If the research protocol is to be revised, the date on which the revised research protocol will come into effect will be specified, and approval will be obtained from an accredited clinical research review committee. After that effective date, the research will be conducted based on the revised research protocol.

1. **Management of deviation from research protocols**

1) When the principal investigator becomes aware that the study is not in conformity with the Clinical Research Act, the implementing regulations or the research protocol (non-conformity), he will promptly report it to the administrator of the implementing medical institution and inform the principal investigator. In addition, when co-investigators become aware of a non-conformity, he/she will promptly report it to the principal investigator.

2) If a specifically serious non-conformity is found, the principal investigator will promptly report it to the accredited clinical research review committee. If there are other collaborating research organizations, will promptly provide information on it.

1. **Periodic reporting**

Every year from the date of submission of the implementation plan to the Minister of Health, Labour and Welfare, the principal investigator will report on the following issues regarding the conducting of this research to the administrator of the implementing medical institution and the accredited clinical research review committee. He will also report the same to the Minister of Health, Labor and Welfare after hearing the opinions of the Authorized Clinical Research Review Committee.

1) The number of research participants.

2) Occurrence of illnesses, defects, etc. caused by this research and their subsequent progress.

3) Status of occurrence of non-compliance related to this research and subsequent actions taken.

4) Assessment of the safety and scientific relevance of this research.

5) Management of conflicts of interest in relation to this research.

1. **Termination of research**

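### Section 9.2 takes seriousness from a reporting scheme in 9.4 whose every class is conditional on suspected causation, so the class of an unrelated death or hospitalisation is undefined or depends on an open-label judgement

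*Protocol*

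**What the plan says.** Protocol section 9.1 has the investigators evaluate diseases and defects identified during the participation period, without a causal limit. Section 9.2 then lists what is documented for each event, including "causal relationship to the study and the course of the disease or defect". It adds a seriousness class: "the severity will be judged as 'serious' or 'non-serious' based on the criteria in section '9.4 Procedures". Section 9.2 has no seriousness definition of its own, and none was found elsewhere in the protocol. Section 15.2.2 speaks of serious health damage but does not define it.

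Section 9.4 sets out who is told of which events and by when. Its four groups open as follows:

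- ① (7 days): "the occurrence of which is suspected to be due to this study and which cannot be predicted"
- ②(a) (15 days): "The following diseases, etc., which are suspected to be caused by this research (excluding those falling under 9.4" (that is, other than those in ①)
- ②(b) (15 days): "The following diseases, etc., which are suspected to be caused by this research and cannot be predicted"
- ③ (periodic report): "Diseases suspected to be caused by this research (excluding those listed in ① and ②")

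**The concern.** Seriousness is normally a property of the outcome of an event; causality and expectedness are separate attributes that decide how fast it is reported. Section 9.2 respects that separation when it records causality as its own item, but then takes seriousness from a section where outcome, causality and predictability are bound together. An investigator who follows the cross-reference as written cannot call an event serious without first suspecting the research.

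That judgement is open-label. Under section 5.3 the investigators themselves confirm the allocation and sign the allocation form, and the comparator is no treatment. Two investigators could class the same hospitalisation differently, and one investigator could class it differently according to arm. Any summary of serious events built on this class would inherit that.

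**Working it through.** The plan gives no figure to reproduce. The check follows the cross-reference from 9.2 into 9.4, lists the conditions of each class, and places test cases in them.

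**Conditions in 9.4**

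| Class | Outcomes listed | Suspected causation required | Unpredictability required |
|---|---|---|---|
| ① | Death; may lead to death | Yes | Yes |
| ②(a) | Death; may lead to death (those not in ①) | Yes | No |
| ②(b) | Hospitalisation or its prolongation; disability; may lead to disability; comparably serious illness; congenital abnormality | Yes | Yes |
| ③ | None (everything else suspected) | Yes | No |

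No row is headed serious or non-serious. Hospitalisation appears once, as "Diseases requiring hospitalisation or prolonged hospitalisation for treatment, etc", under ②(b). The word serious occurs in 9.4 only in item (4) of ②(b), a catch-all under the same two conditions.

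**Test cases**

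1. Hospitalisation, suspected and unpredictable: ②(b).
2. Hospitalisation, suspected but predictable: excluded from ②(b), so it falls to ③, where no outcome criterion separates it from a trivial complaint.
3. Hospitalisation, judged unrelated: no class.
4. Death, suspected and predictable: ②(a). Predictability therefore does not exclude deaths.
5. Death, judged unrelated: no class.

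Cases 3 and 5 will be in the record, because 9.1 and 9.2 collect events without a causal filter, and each needs a serious or non-serious label that the cited criteria do not supply.

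**Scale**

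The documents give no hospitalisation rate. Assume, for illustration only, 5% to 15% per person-year in this age range. Expected hospitalisations = participants × years × rate:

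- lower: 20 × 0.5 × 0.05 = 0.5
- upper: 20 × 0.5 × 0.15 = 1.5

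So about one event is in play, or 0.25 to 0.75 per arm of 10. The textual defect does not depend on this assumption.

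**The case against.** The best case for the plan is that 9.4 does contain usable criteria. It lists the familiar serious outcomes, and item (4) of ②(b) treats them as a benchmark for seriousness. Since 9.2 records causality separately, a sensible reader may take the outcomes as the criteria and the suspected and unpredictable conditions as reporting filters. That reading is reasonable, so it is too strong to say that unrelated events cannot be serious. What remains is that 9.4 never separates outcomes from filters, so the reading has to be supplied by the investigator.

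The predictable-hospitalisation case has no worked example. Section 9.4 counts as predictable what the device summary, protocol or consent document describes, and section 13.1.2 foresees only psychological strain, time constraints and physical strain. The other two documents are not shown. This limb is a gap in the rule, not a demonstrated occurrence.

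A reader might infer three stronger things, and the documents support none of them:

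- *That the control arm's serious count is close to zero by construction.* The causal test refers to the research, not to the app, and section 13.1.2 foresees physical strain from the examinations in controls. Control events can be research-related. The protocol also states no tabulation of serious events by arm; the analysis plan is not at hand.
- *That the review committee never sees unrelated cases.* One item of the periodic report in section 24 is limited to "Occurrence of illnesses, defects, etc. caused by this research and their subsequent progress", but another asks for an assessment of the safety of the research and carries no such limit.
- *That data are lost.* Onset, severity, outcome, causality and course are documented for every event, so an unrelated hospitalisation could be reclassified by outcome later.

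Limiting expedited reports to suspected events is a legitimate choice and is not criticised here.

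**Conclusion.** The point holds as a defect in the cross-reference. The only rule the protocol gives for seriousness points to a section where every class requires suspected causation. Applied literally, unrelated deaths and hospitalisations meet no seriousness criterion; applied charitably, their class is ambiguous. Under the literal reading, the label rests on a causality judgement made with knowledge of the arm.

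Its weight is modest. The study is exploratory and non-invasive with 20 participants, safety is neither a primary nor a secondary outcome, and the underlying records remain complete. It is still worth correcting, because the rule applies each time an event is recorded. The conclusion rests on the wording of 9.1, 9.2 and 9.4 and on no other seriousness definition being in force; one in a separate procedure would reduce this to a wrong cross-reference.

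**What to change.** In 9.2, replace the reference to 9.4 with a statement that an event is serious if it meets any of the outcomes 9.4 already lists: death; may lead to death; hospitalisation or its prolongation; disability; may lead to disability; comparable seriousness; congenital abnormality. State that this applies in both arms, whatever the suspected cause or predictability. Keep 9.4 solely for reporting routes and deadlines. Wherever serious events are summarised by arm, use this outcome-based class, with the separately recorded causality beside it.

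The cost is a short protocol amendment. A few unrelated events will be listed as serious. No visit, staffing, treatment or reporting duty changes.
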